**2-1. Study Object**

The impacts of postpartum depression on mothers and children are well known, and postpartum depression is related to the risks of the suicide of mothers, the delay of development of children, and the mal-social behavior of children. The previous study reported that 12.8% of all mothers were at high risk of postpartum depression. Therefore, it is not only an issue of the mother's health but a big problem with a high impact on children and their social environment. Because the continuous fear about pregnancy or delivery and the lack of social support from families or friends are risk factors for postpartum depression, it is important to provide support for mothers who need it. However, as a shortage of human and time resources in medical facilities and public agencies, it is too challenging to provide face-to-face support for all mothers with worries or questions about pregnancy and their health.

Recently, the research on online medical consultation or online treatment is expanding as support besides medical or public facilities. Online medical consultation services may reduce mothers' worries by providing the chance to consult about their questions about pregnancy and health problems of their children without visiting medical facilities, resulting in reducing risks of postpartum depression. Furthermore, solving the mother's problem with online services may have positive social impacts, such as lowering the burden on mothers and families related to visiting medical facilities.

However, it is unknown that online medical consultation services can reduce the risks of postpartum depression. This study aims to investigate whether providing online medical consultation services can reduce the risks of postpartum depression through a randomized-controlled trial and explore its social impacts.

**2-2. Methods**

(1) Research design

Prospective randomized-controlled trial

(2) Sample size

ⅰ) Numbers of study participants

Intervention group: 360

Control group：360

ⅱ)Rationale of sample size calculation

We calculated the required sample size as 249 in each group to detect differences in the proportion of women who were above a cut-off of the Edinburgh Postnatal Depression Scale: EPDS between 11% and 4% referring to the previous studies and preliminary program, with 5% two-sided significance level and 80% power. Considering the expected attrition rate as about 30%, We set the target sample size as 360 in each group.

ⅲ) Criteria

1. Inclusion criteria

Pregnant women living in Yokohama City whose expected date of delivery was before October 31, 2021.

1. Exclusion criteria

Women who don’t agree the participation.

Women who were not capable of communication in Japanese.

1. Analytic criteria (Participants who met this criteria will be excluded in the supplement analyses)

Miscarriage or stillbirth.

Baby enter the intensive care unit.

Participant get sick and hospitalize after childbirth.

Ongoing treatment of depression, bipolar disorder, or other psychiatric disease at the participation.

(3) Intervention

(1) Invasion to the participants: No

(2) Intervention to the participants: Yes

●Details of the interventions：Online medical consultation services “Syounika Online

/Sanfujinka Online”

In this study, we will provide online medical consultation services “Syounika Online/Sanfujinka Online” which the enterprise Kids Public Inc offers as an intervention. This service is delivered through the LINE platform. Women can consult with obstetrician-gynecologists, pediatricians, and midwives using this mobile service platform in the time women book by chat, call, or video call.

In addition, study participants can use “Josanshi chat Soudan,” in which women can consult with midwives about childcare or feeding by chat without booking after delivery. Furthermore, the enterprise will send the message that women can consult when they want and provide helpful information for women in childcare through the app.

These services provide only consultations; diagnosis, treatments, or intervention at the medical facilities are not included. These services are not invasive and are not competitive with existing medical or public support systems but complementary to them. If medical professionals whom women consult judge women need more aggressive support, the professionals recommend visiting medical facilities or public offices to get help.

(4) Study flow

[figure not shown]
Figure１．Study flowchart.

*Online medical consultation services include “Syounika Online/Sanfujinka Online” and “Josanshi chat Soudan”.

This study is conducted under the project of Yokohama city. The member of the department of health and social behavior, the University of Tokyo, operates this study co-ordinate with Kids Public Inc., Kohoku-ward in Yokohama city, and other wards in Yokohama city.

1. Recruitment

We will recruit eligible pregnant women living in Yokohama city between September 1, 2020, and October 31, 2021, using leaflets or other media to ask them to access the study website. To inform the study information, we will distribute the leaflets with a QR code of the study website at the ward office, at the childbirth classes held or supported by Yokohama city, and at the medical facilities in Yokohama city. In addition, we will announce our study information, the QR code, and the URL of the study website on the official Twitter account, on the official website of Yokohama city, on the official newspaper of Kohoku ward, and by the official letter for pregnant women from Yokohama city. Pregnant women can access the study website through these announcements.

Figure 2. Assumed image of the leaflet.

[figure not shown]

② How to obtain the agreements, get the baseline personal information, and randomize the participants.

Pregnant women will spontaneously access the study website and be checked the eligibility on the website. After that, they read and understand the study protocol details, the offered intervention, randomization, and the deal of their personal information. We will inform the women that the study team of the University of Tokyo, Yokohama city, and Kids Public Inc. will share their minimum required private information to conduct this study. Women who want to participate in this study will agree with the participation and enter their personal information, including name, birthday, mail address, mobile phone number, postal code, expected day of delivery, parity, and family structure, on the website. After sending the agreement, an online system will immediately generate the study ID and 1:1 random allocation to either the intervention group or the control group without using any personal information. Participants will know their random assignment shown on the website and by e-mail.

After allocation, participants will receive an online questionnaire sent by e-mail from the study team of the University and answer it. This questionnaire will ask about baseline participants' information, such as the primary outcome of EPDS, gestational age, loneliness, past mental health problems, income, education, and social support.

Figure 3. Assumed image of the study website.

[figure not shown]

③ Details of information about the intervention group and the control group

1. The intervention group

Pregnant women in the intervention group will be provided the online consultation services, “Syounika Online/Sanfujinka Online” from the participation to four months after delivery, and the services “Josanshi chat Soudan” four months after delivery. Usually, these services need a usage fee; however, study participants can use them free without limitations on the number of times.

<Features of the intervention>

- Users can book any available time and consult anything they want for ten minutes during the service hours, which are Monday through Friday between 6 PM and 10 PM.
- Users can choose preferred methods, including voice calling, chat messaging, and video calling
- Users can also consult with midwives by chat without booking after the childbirth between 12 PM and 6 PM on the 2-3 times open weekday.
- Service provider constantly informs the users at least once a week that users can consult anything if they want through the platform.

Figure 4. The image of online consultation services (Intervention group)

[figure not shown]
　　　
[figure not shown]

Women in the intervention group will get the online survey of EPDS two months after delivery offered by the service provider as a standard service. Women having high scores will be recommended to consult with professionals in the app.

1. The control group

Women in the control group cannot use the online consultation services above. Instead, they can use the website made by the research team of the University, which offers URLs of the useful public websites about pregnancy and childcare. Women in the control group also can get the online voucher after answering the baseline questionnaire.

Figure 5. The Image of the website offering the URLs of the useful websites (Control group)

[figure not shown]

Because this is an effectiveness study to evaluate the services, which have already been introduced in several public agencies or companies, women assigned to the control group can buy the services of their own will, and we will not prohibit it.

④ Online questionnaire of the outcomes three months after delivery

The research team of the University will get the childbirth date of all participants who submit the registration of birth to the public office from the agencies of Yokohama city with the participants’ agreement.

A research member will send an online questionnaire three months after delivery by e-mail. This questionnaire includes the primary outcome of EPDS and other outcomes such as self-efficacy, loneliness, and usage of the medical facilities. Participants will get an online voucher after answering this questionnaire regardless of the assigned groups.

⑤ Analytic methods

This study aims to assess the difference in the proportion of EPDS above the cut-off three months after delivery between the intervention group and the control group. Analyses will be conducted according to the intention-to-treat principle. We will conduct Fisher's exact test for the primary outcome. We will use a t-test or Mann-Whitney U test for the secondary outcomes according to the variable characteristics. The outcomes are bellow.

●Primary outcome

Proportion of the participants with the Edinburgh Postnatal Depression Scale (EPDS) above the cut-off three months after delivery（Cut-off points: nine or above）.

●Secondary outcomes

• Barriers to healthcare access

• Parenting self-efficacy

• Loneliness (the 3-items version of UCLA loneliness scale)

• Usage of the medical facilities besides regular health check

- Daytime visit

- Night, weekend, and emergency visit (outside of the business hours)

- Ambulance usage

• Participant rate to the childcare class

• Any other information needed by Yokohama city

We will conduct subgroup analyses. Subgroups are below.

●Subgroups

• EPSD above or under the cut-off at the participation

• Primipara or multipara

• Income

• Education

• Age (under 18 years old or above)

• With or without partner

• Having past mental health problem or others

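### The plan states intention-to-treat and expects about 30% attrition but has no rule for a missing three-month EPDS, so as written the primary Fisher test compares responders only and is open to non-response bias in either direction

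*Combined protocol and SAP*

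**What the plan says.** Protocol section 2-2 Methods, (4) Study flow, item ⑤ (Analytic methods) states: "Analyses will be conducted according to the intention-to-treat principle". The primary test there is Fisher's exact test on the proportion of women with an EPDS of nine or above. Item ④ takes that EPDS from one questionnaire e-mailed by the University three months after delivery. The delivery date comes from the city: the team "will get the childbirth date of all participants who submit the registration of birth to the public office".

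Section 2-2 (2) Sample size gives the planning figures: "We calculated the required sample size as 249 in each group", for "EPDS between 11% and 4% referring to the previous studies and preliminary program", "with 5% two-sided significance level and 80% power". It then adds: "Considering the expected attrition rate as about 30%, We set the target sample size as 360 in each group". The same section lists pregnancy loss and some other conditions as reasons for exclusion in supplementary analyses only.

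The SAP section adds modified Poisson models for confidence intervals of binary outcomes, and subgroup analyses. Neither the protocol nor the SAP defines the intention-to-treat population, gives a rule for a missing three-month EPDS, or plans a sensitivity analysis for non-response.

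**The concern.** A two-by-two table needs an outcome for every woman in it. Without a rule for missing outcomes, only women who answer can enter, so a comparison labelled intention-to-treat would leave out about three in ten of those randomised.

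Symptoms may affect whether a woman answers, and several features could make that differ by arm:

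- The trial is open: "Participants will know their random assignment shown on the website and by e-mail".
- Only the intervention arm receives provider messages at least weekly, and an EPDS survey at two months with a recommendation to consult for high scorers.
- Only controls receive a voucher for the baseline questionnaire.

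If response is related to EPDS differently in the two arms, the estimated difference and its p-value partly reflect who replied. As the plan stands, a reader of the results could not judge how far.

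**Working it through.** **Inputs.** From section 2-2 (2): 11% vs 4%, two-sided 5% level, 80% power, 249 per arm, about 30% attrition, 360 per arm. From section 2-2 (4) ②: "1:1 random allocation to either the intervention group or the control group". The response rates by EPDS status and the event counts among missing women are assumptions; the documents give none.

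**1. The plan's own figure.** With mean proportion 0.075 and difference 0.07:

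n₀ = [1.96·√(2·0.075·0.925) + 0.8416·√(0.11·0.89 + 0.04·0.96)]² / 0.07² = 221.1

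With continuity correction:

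n = (n₀/4)·[1 + √(1 + 4/(n₀·0.07))]² = 248.8, rounded up to 249.

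This matches the plan. Attrition: 249/0.70 = 355.7, so 356, close to the stated 360.

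**2. Expected loss.** 360 × 0.30 = 108 per arm (216 of 720), leaving 252 per arm. Exact Fisher power at 11% vs 4% with 252 per arm is 82.8%. The plan therefore intends about 250 observed outcomes per arm to carry the test, and power is covered.

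**3. No true effect, selective response in one arm.** Assume 11% in both arms, 70% response overall in each arm, and control response unrelated to EPDS. If intervention-arm high scorers reply at rate r, the low scorers reply at (0.70 − 0.11r)/0.89 and the observed intervention rate is 0.11r/0.70. Exact Fisher rejection at 252 per arm:

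| r | Observed, control vs intervention | Rejects at 5% |
|---|---|---|
| 70% | 11.0% vs 11.0% | 3.6% |
| 60% | 11.0% vs 9.4% | 6.8% |
| 50% | 11.0% vs 7.9% | 18.5% |
| 40% | 11.0% vs 6.3% | 41.6% |

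Total response is 70% in both arms in every row, so equal response rates would not rule the problem out.

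**4. The same selection in both arms.** If high scorers reply at 60%, 50% or 40% in both arms, rejection under no effect stays at 3.4% to 3.6%. Selective response alone does not inflate the error; it must differ by arm.

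**5. The opposite direction.** Let the true rates be 11% vs 4%, with selection in the control arm only and r = 50%. The observed control rate is 0.11 × 0.50/0.70 = 7.9%, so a true difference of 7 points appears as 7.9 − 4.0 = 3.9 points. A real benefit is then understated.

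**6. Tipping point for a result as planned.** Responders 28/252 (control) vs 10/252 (intervention): Fisher p = 0.0036. Let 12 of the 108 missing controls (11%) be events, so control is 40/360. Vary the events among the 108 missing intervention women:

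| Events among 108 missing | Intervention total | p |
|---|---|---|
| 12 (11.1%) | 22/360 | 0.023 |
| 14 (13.0%) | 24/360 | 0.049 |
| 15 (13.9%) | 25/360 | 0.068 |
| 16 (14.8%) | 26/360 | 0.093 |

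Significance is first lost at 15. For comparison, counting every missing woman as an event gives 136/360 vs 118/360, p = 0.18; counting every one as a non-event gives 28/360 vs 10/360, p = 0.004. The unstated rule can decide the result.

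**The case against.** Several stronger readings are tempting, and the documents do not support them.

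- *Fisher's test is the wrong test.* It can be run on all 720 women once a missing-outcome rule exists. What is absent is the rule.
- *The intention-to-treat label is untrue.* The plan does not define the term, and it is often used to mean analysis by allocated arm. The plan meets that sense but does not cover all randomised women.
- *108 women per arm will be lost.* That is a planning allowance, not an observed loss, and the sample size already absorbs it.
- *Non-response will produce a false benefit.* Nothing in the documents shows differential response. The three-month questionnaire comes from the University rather than the service provider, and carries the same voucher in both arms. The inflated rejection rates need high scorers to reply less in the intervention arm only; the reverse pattern would hide a benefit.
- *The birth-registration trigger biases the comparison.* No fallback is stated for women without a registration, so it can add missing data. It applies to both arms alike, and no reason for a difference by arm is apparent.

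It is also fair that a result as planned has some robustness. It survives missing intervention women having the same event rate as missing controls (p = 0.023). Overturning it takes about 14% among missing intervention women, some 3.5 times the 4% in their own responders.

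All of this limits the size and direction of the claim. It does not supply the missing rule.

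**Conclusion.** The point holds in this form: intention-to-treat is stated but not defined, about 30% of outcomes are expected to be missing, and no rule or sensitivity analysis deals with them. As written, the primary analysis is complete-case by allocated arm.

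The possible bias is material but hypothetical. Under the one-sided assumptions in step 3, the chance of a false positive rises from 3.6% to 18.5% or 41.6%; with equal selection in both arms it does not rise, and with the opposite selection the effect is understated. A result as planned tips at 15 of 108 missing intervention women, given 12 of 108 among missing controls. These figures rest on assumed response and event rates and show sensitivity, not expected bias. The concern is bias and the meaning of the label, not power.

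**What to change.** Amend the SAP as follows.

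1. Define the analysis population. State explicitly how women with pregnancy loss are handled, consistently with section 2-2 (2), which excludes them only in supplementary analyses.
2. Pre-specify multiple imputation of the three-month EPDS by arm, analysed with the modified Poisson model already planned. Use first the variables entered before allocation: age (from birthday), parity, expected delivery date and family structure.
3. Repeat the imputation with the baseline-questionnaire variables added: EPDS, loneliness, mental-health history, income, education and social support. Keep this as a separate step. Under section 2-2 (4) ② that questionnaire is answered after women know their arm, and only controls receive a voucher for it, so these variables may themselves be missing or affected differently by arm.
4. Pre-specify a tipping-point analysis that varies the event rate among missing women separately by arm.
5. Report response by arm and the complete-case Fisher result, and do not describe the latter as covering all randomised women.

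The cost is SAP text and some programming; no new data are needed. The downside is more modelling assumptions than a raw comparison, which the tipping-point analysis makes visible.

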**3. Burdens, expected risks, and benefits for study participants.**

(1) Physical and psychological burdens and potential risks.

• Participants don't need any charges for online consultation services except for internet usage or voice call charges.

• Participants need to answer online questionnaires two times, at the participation and three months after delivery. It will take 10 - 15 minutes.

• Personal information will be managed on the server of the service provider strictly. However, there may be psychological burdens that participants feel anxious about the leakage of their information.

(2) Benefits of participants

• All participants will get about ten dollars online vouchers of Amazon inc. when they answer the online questionnaire three months after delivery.

• Participants assigned to the intervention group can use the online medical consultation services and get health information without charge.

• Participants assigned to the control group will get about four dollars online vouchers of Amazon Inc. when they answer the online questionnaire at the time of participation.

(3) Measures to minimize the risks for the participants

• To reduce participants' psychological burden, we will announce that their personal information will be stored with a password lock and used only to collect information related to the research, evaluate social impact, and deliver online medical consultation services.

• Furthermore, we also announce that personal information will be used only by the research team members of the University of Tokyo, public agents of Yokohama city in charge of this study, and the person of Kids Public Inc. in charge of this study.

**4. Informed consent**

We clearly explain the study aim, study flow, randomization, and interventions on the study website. We also state that we will adhere to the "Ethical Guidelines for Medical and Health Research Involving Human Subjects" and "Declaration of Helsinki" on the website. In addition, we announce that participants can decide whether they participate or not of their own will, that they never have a disadvantage by not participating, and that they can withdraw the participation whenever they want.

We consider women to agree to participate in our study by checking the agreement of participation and entering their names, birthday, and mail addresses on the study website. We state the contact mail address on the study website, and we announce participants to send a mail if they want to withdraw their participation.

**5. How to deal with the personal information of the study participants.**

We obey the "Act on the Protection of Personal Information," and we carefully treat the information to protect participants' privacy.

We announce that personal information will be used only by the research team members of the University of Tokyo, public agents of Yokohama city in charge of this study, and the person of Kids Public Inc. in charge of this study. We also announce that their personal information will be used only to deliver online medical consultation services, to conduct this research, and to evaluate the social impact and that we never use other aims nor share other people who do not relate to this study.

As a general rule, during the study periods written in the protocol made by the research member of the University of Tokyo, Yokohama city will agree to conduct the primary and secondary analyses of the anonymous data in this study and to publish Japanese/English articles on the study results after checking the contents to increase the social value of this study.

(1) How to obtain the information of the participants

The information participants enter on the website will be stored on the server of the Google Cloud Platform managed by Kids Public Inc. with encryption and password rock. A research member of the University of Tokyo will get the data of name, birthday, study ID, and mail address with the password needed to conduct the research from a member of Kids Public Inc.

A research member of the University of Tokyo will obtain the baseline and outcome data from the participants by Google forms sent by email to the participants, store in the researcher's Google Drive temporarily, and be managed in the local storage in the data managing room of the University of Tokyo.

After the intervention study period, a member of Kids Public Inc. will provide all anonymous data that participants will enter at the participation to the University of Tokyo research member with a password rock. Finally, a data manager will merge all data using the study ID. An analyst of the research member will conduct the primary and secondary analyses using this data.

All data managed in a data managing room of the University of Tokyo will be stored in the local storage with a password lock and kept in a locker locked by a physical key.

(2) How to deal with the data after the study period

After the study period, all information stored on the server of Kids Public Inc. will be discarded. The data managed at the University of Tokyo will be processed in an anonymous state and kept for a long time to conduct further studies evaluating the social impacts if the participants agree.

